#### Secondary endpoints

Secondary endpoints of the TRIANGLE trial are as follows:Rate of the following:Microscopically complete margin clearance (> 0.1 cm margin clearance, R0(CRM-))Microscopic margin clearance ≤ 0.1 cm (R0(CRM+))Microscopic margin involvement (R1) resections according to the 8th edition of the UICC TNM classificationRate of the following PD-associated postoperative complications within 90 days after the index operation:Postoperative pancreatic fistula (POPF) as defined by the International Study Group of Pancreatic Surgery (ISGPS) [26]Postpancreatectomy haemorrhage (PPH) as defined by the ISGPS [27]Delayed gastric emptying (DGE) as defined by the ISGPS [28]Bile leakage as defined by the International Study Group of Liver Surgery (ISGLS) [29]Lymphatic fistula as defined by the ISGPS [30]Diarrhoea as graded by the Common Terminology Criteria for Adverse Events (CTCAE) version 5.0 [31]All other postoperative complications graded according to the Dindo-Clavien classification [32] within 90 days. This endpoint complements the PD-associated complications evaluated via the above-mentioned ISGPS endpoints, to assess all remaining postoperative complications to establish a risk-benefit assessment of the two interventions.Overall survival within the study period.Local recurrence within the study period.Quality of life (QoL) according to the European Organisation for Research and Treatment of Cancer (EORTC) QLQ-C30 and PAN26 at discharge and during every follow-up visit compared to baseline.Quality of recovery (QoR) according to the QoR-15 questionnaire on postoperative day 5 compared to baseline.Length of primary hospital stay in days from the day of index operation to the day of discharge.Serious adverse events (SAEs) in both groups .

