### Participant timeline {13}

Patients scheduled for elective PD will be screened preoperatively (visit 1). After the patient has given informed consent, the inclusion and exclusion criteria are assessed during the screening visit. Patients fulfilling all the inclusion criteria and none of the exclusion criteria and who consent to take part in the trial are randomised during surgery (visit 2; surgery and randomisation) after the surgeon has obtained certainty that both interventions can be performed in the patient. The results of the pathologic work-up (secondary endpoint) will also be recorded in the eCRF section of visit 2. Patients are planned for follow-up visits on postoperative days 5, 10–12 and 90 (visits 3, 4 and 6) for the evaluation of primary and secondary endpoints. Visit 5 will be performed at discharge. If discharge occurs before visit 3 or 4, the respective postoperative visits (3 or 4) can be omitted. In addition, 6, 12, 18, 24, 30 and 36 months (visits 7–12) after surgery, patients are planned for follow-up visits to evaluate primary and secondary outcome parameters (Fig. 1 and Table 2).

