### Assignment of interventions: allocation

#### Sequence generation {16a}

To ensure an equal distribution of patient characteristics and confounders between the two groups, a randomisation tool will be used. Randomisation will be performed at the patient level with a centralised online randomisation system (www.randomizer.at). The online randomisation procedure provides information regarding the group allocation and a randomisation number. The randomisation sequence is computer-generated and will be stratified by centre and presence/absence of neoadjuvant treatment. Block randomisation will be performed. The randomisation procedure will be performed intraoperatively (after surgical exploration) after the fulfilment of all intraoperative inclusion criteria.

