## Statistical methods

### Statistical methods for primary and secondary outcomes {20a}

The primary outcome disease-free survival is compared between the groups using a Cox proportional hazards model adjusted for the covariates treatment group, age, neoadjuvant treatment, adjuvant treatment as fixed effects and centre as a random effect. It can be expected that applying the Cox proportional hazards model will lead to an increase in power in comparison with a log-rank test. Confounding by other less important prognostic and predictive factors can be assumed to be controlled by the randomised trial design. The significance level is set to 5% (two-sided). The confirmatory analysis is conducted based on the full analysis set (FAS) according to the ITT principle, i.e. all randomised patients are included and analysed in the treatment group as randomised which reflects a treatment policy approach (according to the ICH E9 (R1) addendum). Death, as an intercurrent event occurring after randomisation, is handled by inclusion into the definition of the primary endpoint which reflects a composite strategy.

All secondary outcomes will be evaluated descriptively, and descriptive *p*-values for the corresponding effects will be reported along with 95% confidence intervals. Continuous variables will be described using a number of missing values, non-missing values, mean, standard deviation, median, Q1, Q3, minimum and maximum. For binary or categorical variables, absolute and relative frequencies will be provided. Thereby, binary and categorical variables will be compared by the chi-squared tests, and continuous variables will be compared with *t*-tests. OS will be analysed analogously to the primary endpoint with a Cox proportional hazards model. QoL will be analysed using linear mixed models with baseline score, age, treatment group and the stratification variables as covariates; centre and time point will be included as random effects. Furthermore, the treatment effect for secondary endpoints will be assessed descriptively within several subgroups to identify potential prognostic and predictive factors. Analyses of secondary endpoints will be based on the ITT population. No imputation of missing values will be conducted in the analyses of secondary endpoints.

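### The quality-of-life mixed model, as written, has no patient effect, so its confidence intervals are too narrow and its descriptive p-values too small

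*Protocol article*

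**What the plan says.** The model is in the protocol article, Statistical methods for primary and secondary outcomes {20a}. The fixed part reads: "QoL will be analysed using linear mixed models with baseline score, age, treatment group and the stratification variables as covariates". The random part follows directly: "centre and time point will be included as random effects". Neither that section nor any other names a patient effect or a covariance between scores of the same patient.

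The data are repeated within patients. Secondary endpoints lists the EORTC "QLQ-C30 and PAN26 at discharge and during every follow-up visit compared to baseline". Participant timeline {13} places the later visits at "6, 12, 18, 24, 30 and 36 months (visits 7–12) after surgery". Table 2 marks QoL at screening, at discharge and at visits 7 to 12.

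Sequence generation {16a} says that randomisation is "stratified by centre and presence/absence of neoadjuvant treatment", so the stratification variables in the QoL model are centre and neoadjuvant treatment.

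On the status of the results, section {20a} says: "All secondary outcomes will be evaluated descriptively". It still promises that descriptive p-"values for the corresponding effects will be reported along with 95% confidence intervals". Further details are left to the SAP, which is to be finalised before database closure.

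**The concern.** Random effects for centre and time point let scores be alike because they come from the same hospital or the same visit. They do not let them be alike because they come from the same person. Adjusting for the baseline score removes some of the variation that a patient's scores share, but not the correlation that remains among the later scores.

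Treatment is constant within a patient, so the information on the treatment difference depends largely on the number of patients. A model without a patient term acts as if it depended on the number of questionnaires, and reports a standard error that is too small.

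At stake is how uncertainty about QoL is presented. The article's Discussion says that data on morbidity and patient-reported outcomes are both needed for an informed risk-benefit assessment. It also reports more diarrhoea after extended resection in the preliminary data. Intervals that are too narrow could make a chance QoL difference look established, whichever group it favoured.

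**Working it through.** The plan gives no figure for the QoL model, so there is none to reproduce first.

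**Inputs from the article**
- 270 patients, 135 per group (Sample size {14}).
- Seven post-baseline QoL assessments: discharge and months 6, 12, 18, 24, 30 and 36 (Table 2). It would be eight if the day-90 visit counted as a follow-up visit, but Table 2 does not mark QoL there.
- At least seven centres (Study setting {9}); seven were used.

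**Assumptions, not in the article**
- Residual within-patient correlation ρ, given the model covariates: 0.1 to 0.7.
- Median overall survival of 24 months (exponential), and 10% of questionnaires missed among survivors.

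**Step 1: formula.** For a comparison between patients with m scores each, the true variance is 1 + (m − 1)ρ times the variance that assumes independence. The true standard error (SE) is √[1 + (m − 1)ρ] times the reported one. The type I error of a nominal 5% test is 2[1 − Φ(1.96 / SE ratio)].

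**Step 2: all seven scores, ρ = 0.5.** The variance ratio is 1 + 6 × 0.5 = 4.0, so the SE ratio is 2.0. The type I error is 2[1 − Φ(0.98)] = 33%, and a nominal 95% interval covers 67%. This is an upper case, because many patients will not live to give seven scores.

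**Step 3: allowing for deaths and missed forms.** Discharge is placed at 0.5 months. Survival at the seven time points is then 0.986, 0.841, 0.707, 0.595, 0.500, 0.420 and 0.354, which sums to 4.402. The mean number of scores is 0.9 × 4.402 = 3.96.

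The number of scores differs between patients, so m in the formula becomes E(m²)/E(m). For each visit, multiply its survival probability by the number of earlier visits; the sum is 0.841 + 2 × 0.707 + … + 6 × 0.354 = 10.26. Then E(m²) = 3.96 + 2 × 0.81 × 10.26 = 20.59, and the effective m is 20.59 / 3.96 = 5.20.

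**Step 4: simulation under no treatment effect.** Each setting used 1,500 trials of 270 patients, with centre and time point taken out and no patient term.

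| ρ | SE ratio, formula (m = 5.20) | SE ratio, simulated | Type I error, formula | Type I error, simulated |
|---|---|---|---|---|
| 0.1 | 1.19 | 1.19 | 10% | 11% |
| 0.2 | 1.36 | 1.35 | 15% | 16% |
| 0.3 | 1.50 | 1.50 | 19% | 19% |
| 0.5 | 1.76 | 1.76 | 27% | 28% |
| 0.7 | 1.98 | 1.99 | 32% | 31% |

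Formula and simulation agree. At ρ = 0 the simulated type I error was 5%, so the inflation comes from the correlation alone. With patient-clustered standard errors on the same data it was 4% to 6% throughout.

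**Step 5: other assumptions.**
- Correlation that decays with time (AR(1), 0.5 or 0.7 between adjacent visits): 17% or 27%.
- Median survival of 18 months: 17% at ρ = 0.3 and 25% at ρ = 0.5.
- No deaths (6.3 scores per patient): 23% at ρ = 0.3 and 31% at ρ = 0.5.

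**Step 6: the mixed model itself.** In 60 fits at ρ = 0.5, the model with random centre and time point reported a mean treatment SE of 1.16. The estimates actually varied with an SD of 2.07. A model with a patient intercept reported 1.98, against an SD of 2.01. Only the second is calibrated.

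**The case against.** The strongest reply is that this is one condensed sentence. The analysis will be done in SAS, where a time-point effect is often declared within a subject. Time point as a random effect may therefore be shorthand for the repeated factor within patient, and the SAP may say so. That is possible, and the article does not prove that clustering will be ignored. But the article does not leave the random effects open. It lists them, and the list omits the one that the design needs. A programmer who follows the text would fit the wrong model.

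The second reply is that QoL is secondary and descriptive, with no share of the significance level and no part in the sample size. That stands and limits the severity. It does not excuse the intervals, since a 95% interval should cover at about its stated rate whatever the label on the p-value.

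A reader might also infer more than the article supports:
- *That treating time point as random causes the inflation.* It does not; the missing patient term does. Time point suits the fixed part because the visits are a small planned set, but that is a separate matter.
- *That the model creates false QoL differences.* The fault shown is in the standard error, not in the estimate.
- *That centre is wrongly counted twice.* Read literally, it is both a covariate and a random effect. The primary Cox model in the same section has neoadjuvant treatment fixed and centre random, and the QoL sentence probably means the same. This is untidy wording with no demonstrated consequence.
- *That the lack of a treatment-by-time term is an error.* An average difference over follow-up is a legitimate summary.

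**Conclusion.** The point holds as a mis-stated model for a secondary endpoint. Followed as written, it gives treatment standard errors that are too small: the true value is about 1.2 times the reported one at a within-patient correlation of 0.1, and about 2.0 times at 0.7. The type I error is then about 11% to 31% instead of 5%.

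The direction of the error follows from the design for any positive residual correlation. Its size rests on assumptions that the article does not supply: the correlation, survival and questionnaire completion. At the low end the error rate roughly doubles; from about 0.3 upwards it is close to four times nominal or more.

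A reader might take this as a threat to the trial's main conclusion. It is not: the disease-free survival analysis uses a different model and is unaffected. Severity is moderate.

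**What to change.** Restate the QoL model, in the SAP at the latest, as a repeated-measures mixed model:
- Add a patient random intercept, or an unstructured within-patient covariance across visits.
- Enter time point as a categorical fixed effect.
- Keep baseline score, age, treatment group and neoadjuvant treatment as fixed effects, and enter centre once, as a random effect, in line with the primary model.
- Optionally, add a treatment-by-time term and report the difference at each visit.

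If time point was meant as the repeated factor within patient, one sentence that names the patient as the subject and states the covariance structure would settle the main point.

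The cost is wording and programming. No visit, data item or patient number changes, and the SAP need only be final before database closure.

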### Strategies to improve adherence to interventions {11c}

As the interventions of the TRIANGLE trial (experimental and control groups) are surgical interventions, strategies to improve adherence to the allocated intervention are not needed.

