Intervention effect: Possible intercurrent events and the strategies to handle them are as follows: Death, as an intercurrent event occurring after randomisation, is handled by inclusion into the definition of the primary endpoint which reflects a composite strategy. Patients with incomplete observation time due to loss to follow-up or early drop-out will be censored at the last observation, which reflects a hypothetical strategy. Besides these events, other post-randomisation events (e.g. intervention not as randomised, discontinuation of chemotherapy) will not be considered, thus reflecting a treatment policy approach, which means that the effect of randomised treatment is estimated irrespectively of other post-randomisation events not captured in the primary endpoint definition. This corresponds to the intention-to-treat (ITT) principle.

Summary measure: The summary measure is the adjusted hazard ratio.

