### Sample size {14}

The sample size calculation is based on the primary endpoint disease-free survival. The assumptions are based on a median survival time of 14 months in the control group and 21 months in the treatment group resulting in a corresponding hazard ratio of 0.667 assuming exponentially distributed survival times [7, 16, 33]. To detect the assumed difference using a log-rank test at a significance level of 5% (two-sided) with a power of 80%, a total number of 192 events (i.e. recurrence or deaths) are required for the entire trial. It is expected that applying the Cox proportional hazards model, as described below, will lead to an increase in power. With an accrual period of 30 months and a follow-up period of at least 36 months, and assuming an exponentially distributed drop-out rate of 20% (at 66 months), *n* = 270 (135 per group) patients are needed (based on the approximation formula by Schoenfeld). The sample size calculation was done using ADDPLAN 6.1.1.

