### Methods for additional analyses (e.g. subgroup analyses) {20b}

As a sensitivity analysis in the meaning of the ICH E9 addendum, the primary estimand will also be analysed by the unadjusted Cox proportional hazards model. As supplementary analyses, the primary endpoint will also be evaluated based on the per-protocol (PP) population including only those patients without major protocol violations and based on the as-treated set the same way as in the confirmatory analysis. Furthermore, the treatment effect will be assessed descriptively within several subgroups to identify potential prognostic and predictive factors. In addition, further covariables are included and analysed in the primary analysis model in order to identify further possible influencing factors.

For safety analysis, all SAEs will be analysed via descriptive statistical methods. The safety analysis includes calculation of frequencies and rates of complications and serious adverse events together with corresponding 95% confidence intervals. For comparisons of frequencies between the groups, the chi-square test will be used.

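### Harm is fixed to the as-randomised comparison while DFS also gets an as-treated check; a supplementary as-treated table for complications, diarrhoea and SAEs should be added

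*Protocol article*

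**What the plan says.** In the protocol article, the list under Secondary endpoints includes the 90-day complications specific to pancreatoduodenectomy (diarrhoea among them), all other postoperative complications, and SAEs. The section Statistical methods for primary and secondary outcomes {20a} then sets one population for the whole list: "Analyses of secondary endpoints will be based on the ITT population".

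Methods for additional analyses {20b} provides two further populations, per-protocol and as-treated, but only for the primary endpoint. DFS is to be re-evaluated "based on the as-treated set the same way as in the confirmatory analysis", as a supplementary analysis. The safety paragraph in the same section gives methods (frequencies, rates, 95% confidence intervals, chi-square test) and names no analysis set.

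On patients who do not receive the assigned operation, the Primary estimand section says that "other post-randomisation events (e.g. intervention not as randomised, discontinuation of chemotherapy) will not be considered", which is a treatment-policy approach. Strategies to improve adherence to interventions {11c} says that "strategies to improve adherence to the allocated intervention are not needed". No crossover rate is stated anywhere in the article.

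**The concern.** The trial is meant to deliver a risk-benefit assessment of a more radical dissection, and the Discussion ties one harm, diarrhoea, to that dissection. For a superiority endpoint, dilution by crossover is conservative. For harm it works the other way. A control patient who undergoes the radical dissection and develops diarrhoea counts against control. An experimental patient who undergoes a lesser dissection counts as exposed to the radical one.

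As written, benefit would be shown both by assignment and by operation performed, and harm by assignment only. A surgeon advising a patient wants the risk that goes with the operation done as well as the risk that goes with being assigned to it.

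**Working it through.** **1. The plan's own figure.** The sample size section assumes "a corresponding hazard ratio of 0.667 assuming exponentially distributed survival times" and concludes that "a total number of 192 events (i.e. recurrence or deaths) are required for the entire trial". Schoenfeld's formula gives 4 × (1.960 + 0.842)² / (ln 0.667)² = 31.40 / 0.1640 = 191.4, rounded up to 192. The figure is reproduced, and nothing below affects it.

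**2. Which rule governs harm.**
- Secondary endpoints: complications, diarrhoea and SAEs are on the list.
- {20a}: everything on that list is analysed by ITT, with no exception.
- {20b}: per-protocol and as-treated sets apply to the primary endpoint. The safety paragraph names no set, so the rule in {20a} stands.

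**3. Whether crossover can occur.**
- The Primary estimand section names it as an example of an intercurrent event.
- Section {11b} lets the investigator stop the trial intervention for a patient.
- An as-treated set differs from ITT only if some patients did not receive the assigned operation.
- Against this, Eligibility criteria {10} and the exploration phase allow randomisation only after the surgeon has confirmed during surgery that both operations are feasible.

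**4. Effect on the harm difference.** Inputs from the Discussion (retrospective comparison): diarrhoea pT = 34.4% after the TRIANGLE operation and pC = 14.4% after conventional surgery. Let ce and cc be the shares of the experimental and control arms that receive the other operation, and assume that switching is unrelated to a patient's risk.

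- Experimental arm as randomised: (1 - ce) pT + ce pC
- Control arm as randomised: (1 - cc) pC + cc pT
- Difference: (1 - ce - cc)(pT - pC)

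The crossover rates below are assumptions. Power is for a two-sided 5% comparison of two proportions with 135 per group (normal approximation, pooled variance under the null).

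| Assumed crossover | Experimental | Control | Difference | Power |
|---|---|---|---|---|
| none | 34.4% | 14.4% | 20.0 points | 97.2% |
| 5% each way | 33.4% | 15.4% | 18.0 points | 93.5% |
| 10% each way | 32.4% | 16.4% | 16.0 points | 86.9% |
| 10%, control to experimental only | 34.4% | 16.4% | 18.0 points | 92.9% |
| 10%, experimental to control only | 32.4% | 14.4% | 18.0 points | 94.2% |

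**5. With the earlier single-centre trial's rates** (53.6% v 5.9%, a difference of 47.7 points), 5% and 10% each way give 0.90 × 47.7 = 42.9 and 0.80 × 47.7 = 38.2 points. Power stays at about 100%.

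**6. What an as-treated table would show.** In the retrospective example it recovers the 20.0 points only under the same assumption that switching is unrelated to risk. If tumour extent drives both the change of operation and the complications, it can err in either direction.

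**The case against.** The case against has several parts, and most of it limits the size of the point.

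- **Crossover is not forecast.** A reader might infer that the protocol expects control patients to need the radical dissection, because the control-group section mentions that case. That sentence sets a limit on permitted deviations and predicts nothing. Randomisation during surgery, after both operations are judged feasible and immediately before resection, is a real safeguard. This stands.
- **ITT for harm is not an error.** It estimates harm under the same treatment-policy approach as the confirmatory DFS analysis, so the main results for benefit and harm rest on the same footing. This stands, and ITT should remain the main comparison.
- **The signal would probably survive.** At 5% to 10% each way the diarrhoea excess would usually still be seen, and secondary outcomes are descriptive in any case. This stands.
- **Other harms.** A reader might infer that an excess of fistula, haemorrhage or SAEs would be masked. The Discussion reports comparable morbidity apart from diarrhoea in the retrospective series. In the earlier trial's interim safety analysis it reports no significant difference in fistula or haemorrhage and comparable SAE numbers. There is no established excess to dilute.
- **The analysis plan may add such a table.** It may, and nothing in the article forbids one. But the article is not merely silent: it states the population for secondary endpoints and it states which endpoint receives the as-treated analysis. The asymmetry is therefore a written choice, and this objection does not remove it.

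**Conclusion.** The point holds as a modest improvement to the plan. By its stated rules, complications, diarrhoea and SAEs are analysed as randomised, while DFS alone is also examined by operation performed. Any crossover unrelated to risk shrinks the harm difference by the factor 1 - ce - cc; each 5% in both directions removes a tenth of it.

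The 18 and 16 points are illustrations. They rest on assumed crossover rates, on one retrospective pair of diarrhoea rates, and on switching being independent of risk. The actual rate is unknown and should be low, given the feasibility check.

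The documents do not support the stronger conclusions that crossover is expected, that the ITT harm analysis is invalid, or that the as-treated contrast is the true harm.

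**What to change.** Keep ITT as the main harm analysis. Add to Methods for additional analyses {20b}, in substance: postoperative complications, diarrhoea and SAEs will also be tabulated in the as-treated set, defined by the dissection actually performed as recorded at visit 2, as a supplementary safety analysis; the number, direction and reasons for crossovers will be reported by arm.

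The cost is one sentence and one repeated set of tables. The as-treated set is already planned for DFS, and Table 2 already schedules surgery data at visit 2. Sample size, primary analysis and trial conduct do not change. The drawback is that the added comparison is not protected by randomisation and may be confounded by tumour extent in either direction, so it must be labelled supplementary and read beside the ITT result. If crossover turns out negligible, the two sets of tables will agree and little has been spent.
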